**3.6 Safety**

**3.6.1 Definition of Adverse Event**

Endoscopic findings, subjective symptoms, and objective findings for which clinically relevant changes meeting the following criteria are observed will be considered as adverse events.

1. Subjective symptoms and objective findings will be handled as adverse events if “development of a new abnormality” or “worsening” compared with baseline is observed in the investigation of subjective symptoms and objective findings after the completion of the study. The washout period will be included for subjective symptoms.
2. All cases of death will be handled as adverse events.
3. Adverse events for which a causal relation to the study drug cannot be clearly ruled out will be considered as adverse reactions.

**3.6.1.1 Actions against and handling of adverse events**

All adverse events revealed by endoscopy after administration, as well as subjective symptoms and objective findings will be investigated and recorded. The follow-up investigation of subjective symptoms and objective findings will be performed until symptoms become resolved. The follow-up period will be determined by the investigator.

**3.6.2.1 Handling of adverse reactions**

All adverse reactions revealed by endoscopy after administration, as well as the subjective symptoms and objective findings will be investigated and recorded. The follow-up investigation of subjective symptoms and objective findings will be performed until symptoms become resolved. The follow-up period will be determined by the investigator.

**3.6.3 Method of Evaluation of Adverse Events and Adverse Reactions**

- - - 1. **3.6.3.1 Investigation and recording of items**

1. Name of adverse event
2. Time and date of onset (detection)
3. Highest severity
4. Time and date of resolution
5. Time and date of outcome investigation and outcome (ongoing, resolving, or resolved)
6. Presence or absence, and details of treatment (necessity of treatment and the details of the newly performed treatment)
7. Judgment of a causal relation: The results of judgment of a causal relation between the adverse event and rebamipide will be entered in the investigation process. In particular, if the adverse event and rebamipide are judged to be “not related,” the reason should be clarified.
   - - 1. **3.6.3.2 Classification of the causal relation**

1: Not related

2: Probably not related

3: Definitely related

4: Unknown

**3.6.3.3 Definition of the classification of the causal relation**

1. Not related: A direct cause of the event other than the study drug can be clearly identified.

2. Probably related: The adverse event occurs and resolves with a proper temporal relation with the drug administration or blood (tissue and body fluid) concentration of the drug, and other factors are ruled out.

3. Definitely related: The adverse event occurs and resolves with a proper temporal relation with the drug administration or blood (tissue and body fluid) concentration of the drug, and any of the following is met:

• A similar finding is observed by readministration.

• The dose is confirmed to be toxic according to the measurement of drug concentration in the body.

• The drug sensitivity test shows a positive result on allergic symptoms.

4. Unknown: The above judgment cannot be made owing to the lack of information for the evaluation of a causal relation.

**3.6.3.4 Severity <<definition of severity>>**

1. Mild: The event does not particularly interfere with daily life.

2. Moderate: The event interferes with daily life.

3. Severe: The subject experiences great difficulty in daily living.

**3.6.4 Laboratory Test Values**

**3.6.4.1 Definition of laboratory abnormalities**

If clinically relevant changes meeting the following criteria are observed, laboratory test values will be considered as laboratory abnormalities:

1. Laboratory test values will be handled as laboratory abnormalities if “development of a new abnormality” or “worsening” compared with baseline is observed after the completion of the study.
2. Laboratory test values for which a causal relation to the study drug cannot be clearly ruled out will be considered as adverse reactions.

**3.6.4.2 Handling of laboratory abnormalities**

For all laboratory abnormalities, the following will be investigated and recorded. The follow-up investigation of laboratory abnormalities will be performed until normalization of the laboratory test values is confirmed. The follow-up period will be determined by the investigator. If drug withdrawal becomes necessary, symptoms that the subject notices during the withdrawal period and that may be harmful will be communicated to the investigator, as needed.

**3.7 Statistical Analysis**

**3.7.1 Analysis Method**

**3.7.1.1 Analysis of the subjects’ background before the initiation of the study**

Results are expressed as medians and interquartile ranges for continuous variables and percentages for categorical variables. The characteristics of patients in the placebo and rebamipide groups were compared using the χ2 test or Fisher exact test for categorical variables, whereas quantitative variables were analyzed by the Mann–Whitney U-test. The Wilcoxon signed-rank test (for continuous data) or McNemar test (for ordinal data) was used for comparisons of data between baseline and 8 weeks. Differences with P-values <0.05 were considered significant.

**3.7.1.2 Method of analysis of the primary and secondary endpoints**

The Wilcoxon signed-rank test (for continuous data) or McNemar test (for ordinal data) was used for comparisons of data between baseline and 8 weeks. Differences with P-values <0.05 were considered significant.

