**3.3.5 Method and Period of Administration**

1) Patients with small intestinal damage among those taking Bayaspirin will be randomized into two groups (groups A and B). Capsule endoscopy will be used in the diagnosis of the small intestine. A separately specified controller will perform the allocation.

2) Randomization

Subjects will take the randomly assigned test drug during the study.

Dynamic allocation by using the minimization method will be applied in randomization, and subjects will be allocated to each of the two groups in the study. Drug numbers and information on the allocated groups will be managed by the allocation controller, and will be disclosed when the data are fixed after the completion of the study.

3) Allocated groups and drug administration method:

Group A: Three tablets per dose of control (placebo) tablet (100 mg lactose) will be taken three times daily after every meal.

Group B: Three tablets per dose of rebamipide tablet (100 mg rebamipide) will be taken three times daily after every meal.

4) Administration period: 8 weeks

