**3.3.6 Contents and Schedule of Examination**

**Study design**

**Group A**

**(n=15)**

**Group B**

**(n=30)**

**Ｃａｐｓｕｌｅ　ｅｎｄｏｓｃｏｐｙ**

**pre**

**Ｂｌｏｏｄ　ｔｅｓｔ**

**Objective symptom**

**4 weeks**

**8 weeks**

**Ｓｕｂｊｅｃｔｉｖｅ　ｓｙｍｐｔｏｍ**

**3.3.6 Observation Items**

Subject background: Specified at registration

ID assigned by randomization, date of birth, sex, height, body weight, body mass index, drinking history (years), smoking history (years), underlying disease, complications, and used drugs (drug name, dose, and period of use)

Treatment compliance: Status of the administration of the drug

Hematology: Before administration, after administration (4 weeks), and at the completion of treatment (8 weeks)

Red blood cells (104/μL), white blood cells (104/μL), hemoglobin (g/dL), albumin (g/dL), hematocrit (%), total protein (g/dL), glutamic oxaloacetic transaminase (IU/L), glutamic pyruvic transaminase (IU/L), blood urea nitrogen (mg/dL), creatinine (g/day), iron (μg/dL), and C-reactive protein (μg/dL)

Subjective and objective symptoms: Before administration, after administration (4 weeks), and at the completion of treatment (8 weeks)

Subjective symptoms: Epigastric pain, abdominal distension, anorexia, heartburn, stomach heaviness, nausea, vomiting, belching, etc.

Objective symptoms: Epigastric tenderness, hematemesis, melena, etc.

Small intestinal endoscopy: Before administration and at the completion of treatment (8 weeks)

Stool frequency, abdominal symptoms, etc. (after examination; abdominal symptoms and capsule excretion symptoms will be confirmed)

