**3.4 Evaluation Criteria**

**3.4.1 Primary Endpoint**

Decreasing the number of small intestinal mucosal breaks

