**3.7.1.4 Sample size**

Sample size was estimated based on a previous study showing that the complete healing rate of LDA-induced mucosal breaks was 58% in patients who took misoprostol, a PGE1 analog, for 8 weeks. The following assumptions were made for sample size calculation: (1) the wound-healing effect of a triple dose of rebamipide was equal to that of misoprostol; (2) the complete healing rates in the placebo and rebamipide groups were 20% and 58%, respectively; (3) 10% of patients in each group will either drop out or have unsatisfactory follow-up VCE images. We calculated that at least 30 patients were needed in the rebamipide group to give the study 90% power at a 5% significance level by a test of proportions.

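### The endpoint analysis is fixed as within-patient tests that neither compare the arms nor can use the baseline break count as a covariate, although that count is already collected

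*Protocol*

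**What the plan says.** Protocol section 3.4.1 gives the primary endpoint as "Decreasing the number of small intestinal mucosal breaks". Section 3.4.2 adds complete healing, the Lewis score, hemoglobin and albumin, and safety.

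The data for a baseline-adjusted analysis exist. Section 3.3.5 says "Capsule endoscopy will be used in the diagnosis of the small intestine", and section 3.3.6 (Observation Items) schedules it twice: "Small intestinal endoscopy: Before administration and at the completion of treatment (8 weeks" being its wording. Hemoglobin and albumin are also measured before treatment and at week 8.

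The endpoint method in section 3.7.1.2 is a single rule: "The Wilcoxon signed-rank test (for continuous data) or McNemar test (for ordinal data) was used for comparisons of data between baseline and 8 weeks", with significance at P<0.05. Two-sample tests appear only in section 3.7.1.1, on background before the study: "The characteristics of patients in the placebo and rebamipide groups were compared using the" chi-square or Fisher test, "whereas quantitative variables were analyzed by the Mann–Whitney U-test". Section 3.7.1.4 mentions a test of proportions for sizing. No covariate is named anywhere in the protocol.

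**The concern.** The signed-rank and McNemar tests ask whether patients changed between baseline and week 8. In a placebo-controlled trial the question is whether they changed more on rebamipide than on placebo. Section 3.7.1.2 does not ask it, and its tests cannot be extended to use baseline as a covariate.

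Baseline matters for this outcome. The fall in the count is capped by the starting count: a patient with 1 break can lose at most 1, and a patient with 15 can lose 15. Inclusion criterion 6 requires only that small intestinal damage be seen and sets no minimum or maximum count, so low and high counts can both enter. With 15 placebo and 30 rebamipide patients, a few high counts in one arm can move an unadjusted comparison. If section 3.7.1.2 is corrected by borrowing the Mann-Whitney test from section 3.7.1.1, the arms will be compared but information already collected will go unused.

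**Working it through.** **Inputs from the protocol.** Arms of 15 and 30 (section 3.3.6, study design); 10% loss, healing of 20% v 58%, 5% level and 90% power (section 3.7.1.4). Evaluable patients: 15 × 0.9 = 13.5 and 30 × 0.9 = 27. Not given: the count distribution, its SD, the effect on the count, and the baseline-to-week-8 correlation ρ.

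**1. The plan's own figure.** For two proportions at 1:1, one-sided 5%, mean proportion 0.39:

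n = [1.645·√(2·0.39·0.61) + 1.282·√(0.16 + 0.2436)]² / 0.38² = (1.135 + 0.814)² / 0.1444 = 26.3, so 27; and 27/0.9 = 30.

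The stated 30 is reproduced, but only as 1:1 and one-sided; two-sided gives 33, or 37 after loss. At 13.5 v 27, two-sided, the pooled proportion is 0.453 and power is Φ[(0.38 − 1.96·0.1659)/0.1445] = Φ(0.38) = 65%. None of this turns on covariates, but it shows that there is little precision to spare.

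**2. What the stated tests can show.** Simulation with no drug effect, 14 v 27 patients, the same spontaneous fall of 0.3 to 0.7 SD in both arms (assumed) and ρ of 0.3 to 0.7:
- signed-rank test significant in the rebamipide arm: 23% to 99% of trials;
- significant in that arm alone: 14% to 40%;
- Mann-Whitney test of change between arms: 4% to 5%.

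So the arm comparison has to be added before its precision can be discussed.

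**3. What adjustment adds, closed form.** With equal variances, the variance of the arm difference relative to an unadjusted week-8 comparison is 1 for week 8, 2(1 − ρ) for change and 1 − ρ² for ANCOVA. Take an assumed effect of 0.8 SD. The standard error is √(1/13.5 + 1/27) = 0.333, so 0.8/0.333 = 2.4 and power is Φ(2.4/√variance − 1.96):

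| ρ | week 8 | change | ANCOVA |
|---|---|---|---|
| 0.3 | 67% | 53% | 71% |
| 0.5 | 67% | 67% | 79% |
| 0.7 | 67% | 87% | 92% |

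**4. The same question with counts.** Simulation, 3,000 trials per setting, 13 v 27, two-sided 5%. Baseline is 1 plus a negative binomial count (mean 4, size 2 or 0.7). The week-8 count is Poisson-gamma with mean proportional to baseline, and arm multipliers are solved to give 20% v 58% with no breaks. At frailty variances 0.5 and 1 (rank correlation 0.47 to 0.68):
- Mann-Whitney on change: 71% to 87%;
- Mann-Whitney on the week-8 count: 85% to 89%;
- Quade rank ANCOVA: 93% to 94%.

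The gain is about 6 to 22 points over change and 3 to 9 over the week-8 count. The top of the first range comes from one setting (size 2, variance 0.5). At variances 2 and 4 (correlation 0.2 to 0.45) the gain is about 1 to 5 points. Type I error of the rank ANCOVA was about 5%.

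Steps 3 and 4 differ over change at weak correlation. In step 3 subtracting baseline then adds noise. In step 4 weak correlation comes from large extra variation at week 8, which swamps the baseline, so both gains shrink.

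**5. Where adjustment is fragile.** Expected healed placebo patients: 0.20 × 13 = 2.6, or about 3. The chance of none is 0.8¹³ = 5.5%, and ordinary logistic regression breaks down there. For the count, the Wald test from negative binomial regression rejected in about 4% to 10% of null trials at 13 v 27, and the model failed to converge in up to 14%.

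**The case against.** The strongest objection is that covariate choice is commonly left to the SAP, which is not at hand, so a missing covariate is no finding. As to the omission alone, that stands. But section 3.7.1.2 is not silent: it states the endpoint method, and a SAP that compared the arms with baseline adjustment would have to replace that method rather than fill a gap.

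A reader might infer that a planned comparison of the arms loses power. The protocol does not support this. Section 3.7.1.2 plans no arm comparison; the Mann-Whitney, chi-square and Fisher tests are for background characteristics, and the test of proportions is for sizing.

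A reader might also infer that chance baseline imbalance is left uncorrected. That is too strong. The endpoint is a decrease and the tests are paired, so baseline is each patient's own comparator, and a change score corrects imbalance in part. It does so imperfectly because of regression to the mean and the cap on the fall. Section 3.3.5 adds that "Dynamic allocation by using the minimization method will be applied in randomization"; its factors are not named, so balance on break count can be neither assumed nor ruled out.

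It also stands that every gain rests on assumed counts, that a week-8 mean proportional to baseline favors adjustment, and that the protocol calls the study an exploratory pilot.

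**Conclusion.** The point holds in a limited form. The stated endpoint analysis neither compares the arms nor can use the baseline break count, and a concrete better method is available from data already collected. The arm comparison is the substantive correction; baseline adjustment is a refinement of it and a free improvement.

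The gain cannot be derived from the protocol. Under the assumptions in steps 3 and 4 it is worthwhile at moderate correlation and small when correlation is weak. The only protocol inputs to the simulation are the arm sizes, the 10% loss and the assumption that "the complete healing rates in the placebo and rebamipide groups were 20% and 58%, respectively". The figures support rank ANCOVA for the count. They do not support every baseline-adjusted model equally: negative binomial regression with an ordinary Wald test and ordinary logistic regression for healing are not safe primary choices at 13 v 27.

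**What to change.** Rewrite section 3.7.1.2 as follows.

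- **Primary:** compare rebamipide with placebo on the week-8 break count, adjusted for the baseline count by rank ANCOVA (Quade). Rank both counts across all patients, regress the week-8 ranks on the baseline ranks, and compare the residuals between arms. Report medians and interquartile ranges by arm alongside.
- **Lewis score, hemoglobin, albumin:** the same method, each with its own baseline value.
- **Complete healing:** compare the arms by an exact test. Any baseline adjustment is a sensitivity analysis only, by a small-sample method.
- **Signed-rank and McNemar results:** keep as descriptive.
- Do not list ordinary Wald negative binomial regression as an equal primary option.

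The cost is wording in one section and a few lines of code, with no new patients, visits or procedures. The small downside is a result slightly harder to describe than a median change.

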**3.4.2 Secondary Endpoints**

1) Complete healing of small intestinal mucosal breaks

2) Improving the Lewis score

3) Improving hemoglobin and albumin levels

4) Safety evaluation

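### McNemar's test is labelled as a test for ordinal data, and complete healing, the endpoint that sizes the trial, is left without a valid rebamipide-versus-placebo test

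*Protocol*

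**What the plan says.** Protocol 3.7.1.2, headed as the method for the primary and secondary endpoints, consists of one rule and a 5% threshold: "The Wilcoxon signed-rank test (for continuous data) or McNemar test (for ordinal data) was used for comparisons of data between baseline and 8 weeks". Section 3.7.1.1, on patient background, contains the same sentence. The part at issue in both is "McNemar test (for ordinal data) was used for comparisons of data between baseline and 8 weeks".

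The endpoints that the rule must serve are:
- **Primary (3.4.1):** "Decreasing the number of small intestinal mucosal breaks", a count.
- **Secondary (3.4.2):** "Complete healing of small intestinal mucosal breaks", a yes/no outcome; "Improving the Lewis score"; "Improving hemoglobin and albumin levels"; and safety.

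A between-group test for categorical data does appear in 3.7.1.1, but for baseline comparability: "The characteristics of patients in the placebo and rebamipide groups were compared using the χ2 test or Fisher exact test for categorical variables". Section 3.7.1.4 sizes the trial on complete healing, 20% on placebo against 58% on rebamipide, by a test of proportions.

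**The concern.** McNemar's test compares two paired proportions and uses only the discordant yes/no pairs. It is not a test for ordered categories, so the stated rule matches a test to a data type that it cannot take.

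The practical consequence falls on complete healing. As written, this endpoint is neither continuous nor ordinal and no test is assigned to it. If the label is silently corrected to binary, the assigned test asks whether patients within one arm changed from baseline. The trial is randomized and placebo-controlled, and its size was set to detect a difference between arms in this endpoint. An analyst following 3.7.1.2 would not produce the comparison for which the trial was sized.

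**Working it through.** **1. Match each endpoint to the rule.**

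| Endpoint | Data type | Branch of 3.7.1.2 |
|---|---|---|
| Number of mucosal breaks | count | Wilcoxon signed-rank |
| Lewis score | numerical score, no categories defined | Wilcoxon signed-rank |
| Hemoglobin, albumin | continuous | Wilcoxon signed-rank |
| Complete healing | binary | none literally; McNemar if ordinal means binary |

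Complete healing is the only efficacy endpoint that McNemar's test could serve.

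**2. Confirm that the sizing test is a two-group test.** Inputs from 3.7.1.4: p1 = 0.20, p2 = 0.58, 5% level, 90% power, 10% loss. With equal arms and pooled variance under the null:

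n = [z_α·√(2·p̄·(1−p̄)) + z_β·√(p1(1−p1) + p2(1−p2))]² / (p2−p1)²

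Here p̄ = 0.39, 2·p̄·(1−p̄) = 0.4758, p1(1−p1) + p2(1−p2) = 0.16 + 0.2436 = 0.4036, and (p2−p1)² = 0.1444.
- One-sided (z_α = 1.645, z_β = 1.282): (1.135 + 0.814)² / 0.1444 = 26.3, so 27 per arm; 27/0.9 = 30. This is the stated figure.
- Two-sided (z_α = 1.960): (1.352 + 0.814)² / 0.1444 = 32.5, so 33 per arm; 33/0.9 = 36.7, so 37.
- A single-arm test of 58% against a fixed 20% needs only 11.5 (one-sided) or 13.9 (two-sided) patients before loss, 12.8 or 15.4 after.

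The 30 is therefore a between-group calculation. It is reproduced with equal arms and a one-sided test. The protocol does not state the sidedness.

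**3. What McNemar's test does if the label is read as binary.** Assume every patient has breaks at baseline. (Inclusion criterion 6 in 3.1.1 requires small intestinal damage and does not say breaks.) Presence of breaks can then change in one direction only. With k patients healed in an arm and none changing the other way, the exact two-sided P is 2 × 0.5^k:
- k = 5: 2 × 0.03125 = 0.0625
- k = 6: 2 × 0.015625 = 0.031

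Six healed patients give significance whatever happens in the other arm. The protocol does not say which form of the test is meant. Without continuity correction the chi-square statistic is k²/k = k, which passes 3.84 already at k = 4, so the exact form is the more cautious one.

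**4. How often that happens without any drug effect.** Give both arms the protocol's 20% placebo healing rate and use the group sizes in the study design scheme (3.3.6: 15 placebo, 30 rebamipide). From the binomial distribution:
- P(6 or more healed | n = 30, 20%) = 0.57 (0.46 if 27 are evaluable)
- P(6 or more healed | n = 15, 20%) = 0.06

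The chance that the rebamipide arm is significant and the placebo arm is not is 0.57 × (1 − 0.06) = 0.54, although the arms do not differ. The contrast comes from the arm sizes alone.

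**The case against.** The strongest reply is that ordinal is a slip. Every other efficacy endpoint goes to the Wilcoxon branch, so the McNemar branch was presumably meant for complete healing, and changing one word gives that endpoint a valid paired test. That reading is plausible, and it means the statement that the endpoint has no test holds only on the literal wording. It does not remove the problem, because the corrected rule still makes no comparison between arms.

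A second reply is that the chi-square or Fisher test in 3.7.1.1 was meant to carry over, or that a statistical analysis plan supplies the test. The text ties those tests to patient characteristics, while 3.7.1.2 states its own, different rule for endpoints. A later plan could add detail, but the protocol's rule would still be wrong as it stands.

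A reader might also infer that graded outcomes must be cut into two classes at an unstated point, with loss of power and a free choice among cuts. The documents do not support this. No graded efficacy endpoint is defined, the Lewis score is given without categories, and the symptoms in 3.3.6 have no grading scale. The graded item in 3.6.3.4 (for example "Moderate: The event interferes with daily life") is recorded per adverse event and is not a baseline and 8-week pair. Nothing in the protocol would have to be collapsed.

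**Conclusion.** The label is wrong in both 3.7.1.1 and 3.7.1.2. On either reading, 3.7.1.2 does not give complete healing a test that compares rebamipide with placebo, although 3.7.1.4 sizes the trial on exactly that comparison. That conclusion rests on the text alone.

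The figures show why relabelling alone is not enough: a within-arm P of 0.031 from 6 healed patients, reached with probability 0.57 in an arm of 30 at a 20% healing rate and 0.06 in an arm of 15. They assume breaks at baseline in all patients, the exact two-sided test and complete follow-up. If some patients have no breaks at baseline the figures change, but the test remains a within-arm one.

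**What to change.** - **In 3.7.1.2,** state that complete healing at 8 weeks is compared between the rebamipide and placebo groups with Fisher's exact test (or the chi-square test), and state whether the test is one- or two-sided.
- **In 3.7.1.1 and 3.7.1.2,** describe McNemar's test as a test for paired binary data, used only as a within-arm description of change from baseline.

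The cost is a few sentences, with no added patients, visits or data. Naming the test also shows what the planned 15 and 30 patients can deliver. For 20% against 58%, before losses, two-sided power is about 70% by the normal approximation and 62% by Fisher's exact test, below the 90% quoted in 3.7.1.4. That shortfall is a separate sizing question, neither caused nor solved by this change.
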